### Sample size

There are around 130 000 new diagnoses of the six included cancers in the UK annually.^31^ As each of our six cancer sites has different proportions diagnosed at an early stage, the sample size calculation is based on a relative improvement in staging, using an OR of 0.8 for a cancer being diagnosed at stage 3/4 in the intervention arm compared with the control arm. This difference is quite large and equates to an absolute reduction of 4.8% in the intervention arm as an incidence-weighted figure across the six cancers. A much smaller improvement would still be clinically valuable but would necessitate an impossibly large trial.

For the inflation factor we have used an intracluster correlation coefficient based on our previous work, of 0.05.^32^ An average cluster size of 23 patients with a diagnosed cancer with recorded stage during 2-year follow-up is expected, with a coefficient of variation for cluster size of 0.7, giving a design effect of 2.66. For an individually randomised trial with 90% power and an α threshold of 0.05, the sample size would be 2049 patients per arm. Adding in the design effect, this becomes 5497 patients, requiring 239 practices per arm, and 478 practices in total. Owing to changes in practice structure (such as practice mergers, closures or divisions), we anticipate the loss of up to 10% of recruited practices over the course of the trial; to account for this we will recruit a target of 530 practices overall, expecting 12 190 patients to be diagnosed with cancer in total.

### Practice recruitment

A total of 530 primary care practices across England will be recruited, supported by the National Institute for Health Research Clinical Research Network and strategic media releases to raise awareness of the trial. Practices that are proposing a split or a merger are not eligible for the trial, as the practices before or after the change night have been allocated to different arms in the trial. A method for identifying and managing unanticipated splits or mergers during the active phase of the trial is shown in online supplemental appendix B.

Patients are not being recruited into this trial—patient consent is not being sought for the use of the eRATs during the consultation. This is because eRATs are essentially an extension and enhancement of existing diagnostic tools already available to the GP to support their clinical decision-making. Other randomised controlled trials of interventions in primary care have taken this approach,^33^ including the feasibility trial of the oesophago-gastric eRAT.^14 34 35^ To promote patient awareness of the practice’s participation in the Electronic RIsk-assessment for CAncer (ERICA) trial, including requesting practices to add it to their websites and any social media feed. A selection of patients will be recruited to the nested process evaluation and health economics studies (see below and online supplemental appendices C and D).

#### Randomisation

Practices will be randomised using a 1:1 ratio into one of two trial arms: usual diagnostic care (control) and usual diagnostic practice plus access to the suite of eRATs, as the intervention. Randomisation will be computer-generated and web-based, conducted by an independent member of staff at the Exeter Clinical Trials Unit (ExeCTU), overseen by the CTU statistician (not the trial statistician). To promote balance between the trial arms in practices’ use of the 2-week wait system, and therefore propensity to refer to secondary care, we will minimise randomisation by age–sex standardised 2-week wait referral ratio (the best available proxy) in national tertiles. We will use simple randomisation to allocate the first 50 practices (~10% of the total target), and then apply minimisation by 2-week wait referral ratio tertile, taking into account the previous allocations to inform the minimisation algorithm. All allocations using the minimisation algorithm will retain a stochastic element, aimed at promoting allocation concealment.

The data analysis will be carried out by the trial statistician and health economist, blinded to treatment allocation, and all primary outcome data are objective assessments of clinical outcome. Staging (the primary outcome) will be performed by pathologists unaware of trial participation or allocation. However, given the nature of the intervention, it is not possible to blind GPs or the GP practice to treatment allocation.

### Outcome measures

#### Primary outcome

Outcome measures will be captured at patient level, using data routinely collected by the National Cancer Registration and Analysis Service (NCRAS). The primary outcome is whether a patient is diagnosed at stage 1 or 2 (early) or stage 3 or 4 (advanced). This division of staging is commonly used and is a targeted metric in the 2019 NHS Long Term Plan—for stage 1 and 2 cancers (for all staged cancers other than non-melanoma skin cancer) at diagnosis to comprise 75% of the total by 2028. The current UK overall incidence-weighted percentage of early stage at diagnosis was 55% in 2018, though for the six eRAT cancers, it is 35%.^36^

#### Secondary outcomes

A range of secondary outcomes will be examined:

The binary stage at diagnosis of a further six cancers without eRATs will be identified from NCRAS, and compared between intervention and control practices. This is to investigate the possibility of a ‘spillover’ effect whereby eRATs are associated with increased diagnostic activity beyond the eRAT cancers.The practice’s number of patients diagnosed with the six eRAT cancers combined, and the total number of cancer cases, from NCRAS.The number of patients investigated or referred under the 2-week wait system for the six eRAT cancers combined, and in total, from Cancer Waiting Times data.Route to diagnosis from the Routes to Diagnosis Dataset,^18^ which uses Hospital Episode Statistics data. This will be categorised into four possible routes: emergency attendance, 2-week wait referral, GP referral and ‘other’. We will collect this information for each of the six eRAT cancers, and for the six comparator non-eRAT cancers.The 2-week wait performance measures, from Cancer Waiting Times data, for the six eRAT cancers combined, and for all cancer referrals:Whether a patient on a 2-week wait pathway received a diagnosis of cancer. When aggregated, for example at the practice level, and expressed as the proportion of patients who received a cancer diagnosis, this is known as the conversion rate.The duration between 2-week wait referral and diagnosis of cancer in days.Whether patients referred on a 2-week wait referral and who received a cancer diagnosis were diagnosed within 28 days, the Faster Diagnosis Standard (introduced in 2022).Detection rate—the proportion of a practice’s cancers which are identified via the 2-week wait pathway.Survival measures (from date of diagnosis): 30-day; 1-year (identified from NCRAS). 5-year survival will also be reported, but the main trial will report at 30 days and 1 year, with 5-year data being a subsidiary report. These outcomes will use all-cause mortality data from the Office for National Statistics.Adverse events (using data from the Diagnostic Imaging Dataset): these are expected to be few, and largely related to complications from hospital investigation, such as colonoscopy. There is no mechanism for adverse events to be collected using routine data. We will, however, estimate any change in the expected number of adverse events from imaging investigations (colonoscopies, sigmoidoscopies, upper gastro-intestinal endoscopies, chest X-ray examinations, abdominal ultrasound scans and abdominal CT scans) through investigating any change in the rate of these investigations in intervention practices relative to control practices (see data analysis section). Potential adverse psychological consequences of being labelled with ‘possible cancer’ will be further explored in the process evaluation.

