### Objectives

The overarching aim of the trial is to assess the clinical and cost-effectiveness of using eRATs for six cancer sites—colorectal, lung, bladder, kidney, oesophago-gastric and ovarian cancers—compared with usual care for patients in general practice. Our hypothesis is that provision of eRATs will expedite the diagnosis of symptomatic cancer resulting in better cancer outcomes.

The primary objective is to compare the effects of using eRATs (vs usual care) on the percentage of patients with a newly diagnosed cancer at one of the six sites whose cancer is staged as being stage 1 or 2 (vs stage 3 or 4).

A secondary objective is to investigate differences in the stage at diagnosis of a further six cancers without eRATs (combined): breast, melanoma, prostate, non-Hodgkin's lymphoma, larynx and uterus. This is to investigate the possibility of an effect whereby eRATs are associated with increased diagnostic activity beyond the eRAT cancers. We will also investigate differences in the number of patients diagnosed with the six eRAT cancers combined, and the total number of cancers (excluding non-melanoma skin cancer) diagnosed, use of the 2-week wait referral system (the main pathway for urgent investigation of possible cancer in England) or equivalent for the six eRAT cancers combined, and across all cancers; the routes to diagnosis for each of the six eRAT cancers,^18^ and for the six comparator non-eRAT cancers; the proportion of patients on a 2-week wait pathway receiving a diagnosis of cancer; whether a patient on a 2-week wait pathway has a diagnosis of cancer established (or refuted) within 28 days; 30-day and 1-year survival for those with cancer; the rate of cancer investigations—namely colonoscopies, sigmoidoscopies, upper gastro-intestinal endoscopies, chest X-ray examinations, abdominal ultrasound scans and abdominal CT scans. We will also conduct parallel cost-effectiveness analyses, service delivery modelling and a process evaluation.

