Mixed-effects logistic regression models with a random intercept for practice will also be fitted for the other secondary binary outcomes; route to diagnosis, conversion rate and timeliness. These models will include trial arm as a practice-level effect, and will adjust at the patient level for age, sex and quintile of the IMD income domain, and at the practice-level for the minimisation variable (national tertile of age–sex standardised 2-week wait referral ratio). These analyses will also adjust at the patient level for cancer site (routes to diagnosis analyses) or for referral type (2-week wait analyses) as appropriate. The models will be further adjusted as in the main outcome variable analysis.

Time-to-event secondary outcomes (length of waiting time, survival) will be analysed using mixed-effects parametric survival models with a random intercept for practice, and all other variables added as fixed effects. These models will include trial arm as a practice-level effect, and will adjust for the same patient-level factors as described above (waiting times adjusted for referral pathway rather than cancer site as above), and the practice-level minimisation variable (national tertile of age–sex standardised 2-week wait referral ratio). The models will also use the same adjustment as the primary outcome measure. An appropriate distribution to model the baseline hazard will be used, as determined by a comparison of the Akaike information criteria under different distributions.^38^

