### Nested studies

#### Health economics

We will estimate the cost and cost-effectiveness of the eRATs versus usual diagnostic practice using the primary perspective of the NHS and personal social services (ie, third-party payer). We will estimate the cost-effectiveness of the intervention based on the primary outcome and secondary survival outcomes (30 day and 1 year; 5-year survival will be a subsidiary report) for the six cancer sites with eRATs and report the results using the latest guidelines.^39^ For colorectal, lung and ovarian cancers we will use decision analytic models to combine data from the within-trial analysis of ERICA intervention on costs and benefits, with longer estimates derived from the evidence synthesis of the costs and benefits of stage of diagnosis and disease progression to estimate the cost per quality-adjusted life-year over the longer term.^40^ For fuller details see online supplemental appendix C.

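### Survival is timed from diagnosis, a date the intervention is meant to bring forward, so lead time can bias the 30-day and 1-year comparison and the economic analysis that uses it; the primary outcome is unaffected

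*Protocol article*

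**What the plan says.** All references are to the protocol article.

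- **Time origin (Secondary outcomes).** "Survival measures (from date of diagnosis): 30-day; 1-year (identified from NCRAS". Five-year survival is to follow in a subsidiary report. On the source of deaths: "These outcomes will use all-cause mortality data from the Office for National Statistics".
- **Population (Objectives).** The outcome is "30-day and 1-year survival for those with cancer", so only people who receive a diagnosis contribute.
- **Expected effect of the intervention (Objectives).** "provision of eRATs will expedite the diagnosis of symptomatic cancer resulting in better cancer outcomes".
- **Model (Data analysis).** "Time-to-event secondary outcomes (length of waiting time, survival) will be analysed using mixed-effects parametric survival models with a random intercept for practice". The models "will adjust for the same patient-level factors as described above": age, sex, deprivation quintile and cancer site. They also include the minimisation tertile and the same further practice-level adjustment as the primary analysis.
- **Use (Health economics).** "We will estimate the cost-effectiveness of the intervention based on the primary outcome and secondary survival outcomes", at 30 days and 1 year, for the six sites with eRATs.

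**The concern.** Practices are randomised, but diagnosis happens afterwards and is the event the intervention aims to bring forward. If it succeeds, some intervention-arm patients start their survival clock earlier in the same course of disease. A death on an unchanged calendar date then falls later on that clock, and measured survival rises although nobody has lived longer. Randomisation does not remove this, because the shift is an effect of the allocation. Adjusting for age, sex, deprivation and cancer site does not remove it either, because none of these records how far the origin has moved.

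Two things are at stake. A better survival figure in the intervention arm could not be told apart from lead time. The same figure also enters cost-effectiveness as a measure of benefit.

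**Working it through.** The article states no survival rate, survival effect or power for survival, so there is no survival figure of the plan's to reproduce. The check holds every date of death fixed and moves only the date of diagnosis.

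**Inputs from the article.** Origin at diagnosis; horizons of 30 days and 1 year; 12,190 patients expected with cancer (530 × 23); design effect 2.66 from an intracluster correlation of 0.05, mean cluster size 23 and coefficient of variation 0.7. The design effect reproduces: 1 + ((1 + 0.7²) × 23 − 1) × 0.05 = 2.6635.

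**Assumed inputs (not in the article).** Control 1-year survival, lead time L, share f of intervention-arm patients expedited, shape of the survival curve, and the same people diagnosed in both arms.

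**Formula.** With no death postponed, measured survival in the intervention arm is S_int(t) = (1 − f) × S(t) + f × S(t − L), with S(t − L) = 1 when L ≥ t.

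**1-year survival, one-month lead.** With a constant hazard and S(12 months) = 0.60, S(11 months) = 0.60^(11/12) = 0.626. The full shift is 2.6 points.

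- f = 10%: 0.10 × 2.61 = 0.26 points
- f = 25%: 0.25 × 2.61 = 0.65 points
- f = 100%: 2.6 points

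**Other leads, same 60% baseline and constant hazard (points gained at 1 year).**

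| Lead | 10% expedited | 25% expedited | All expedited |
|---|---|---|---|
| 14 days | 0.1 | 0.3 | 1.2 |
| 30 days | 0.3 | 0.6 | 2.6 |
| 60 days | 0.5 | 1.3 | 5.3 |
| 90 days | 0.8 | 2.0 | 8.1 |

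**30-day survival.** At the same hazard, S(30 days) = 0.60^(30/365) = 0.959, that is, 4.1% dead by day 30. An expedited patient with a lead of 30 days or more cannot be a 30-day death in this calculation. The spurious gain is therefore f × 4.1: about 0.4 points at 10% and 1.0 at 25%.

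**Varying baseline and shape.** Take 1-year survival of 50%, 60% or 70%, a constant hazard or a Weibull curve with shape 0.6, and 25% expedited by 30 to 90 days. The 1-year gain is then about 0.3 to 2.3 points and the 30-day gain about 0.7 to 3.6 points. With 10% expedited, or with a 14-day lead in up to 25%, the 1-year gain stays under 1 point.

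**Chance of a false positive.** The effective number per arm is 12,190 / 2 / 2.6635 ≈ 2,288. Using a simple comparison of two proportions, and borrowing the design effect meant for stage, the chance of a significant 1-year benefit with no death postponed is about 4% to 35% in the 25% scenarios. The nominal figure in that direction is 2.5%.

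**Contrast with an origin that cannot move.** If deaths are counted in the registered population from the common start of 1 April 2022, fixed dates of death give a between-arm difference of exactly zero under lead time alone.

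**The case against.** The strongest reply is that this is one of several secondary outcomes and that the size is wholly assumed. That stands. The documents also point away from a lead in every patient: prompts need coded features, age 40 or over and a risk of at least 2%; they appear only when a registered user opens the record; a practice qualifies with half of its GPs agreeing to use the tool; and some cancers arise through screening or emergency presentation. A reader might take the all-patients figures as the expected bias. The article does not support that; they mark only the upper bound on the share.

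A reader might also infer that the trial's main conclusion is compromised. It is not: the primary outcome is stage, and neither it nor the sample size or primary analysis uses survival time.

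Third, a reader might infer that no correction exists anywhere. That cannot be claimed. The analysis plan and the economic appendix are not shown and could contain a correction or a caveat. What this article does fix is the origin, the type of model and the economic use.

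There are partial mitigations. A lead of weeks matters proportionately less at 5 years. The planned cancer counts allow arm-dependent ascertainment to be examined. For colorectal, lung and ovarian cancers the long-term models also draw on external evidence about stage and progression, so survival is not their only driver. None of these corrects the 30-day and 1-year contrast, which is the one carried into the within-trial economics.

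**Conclusion.** The point holds as a bias in a secondary comparison and in one economic input. The direction follows from the plan's own hypothesis: if diagnosis is expedited, survival from diagnosis is shifted towards benefit even with no death postponed. The size is unknown. At 60% 1-year survival, constant hazard and a one-month lead it runs from about 0.26 points (10% expedited) through 0.65 (25%) to 2.6 (all), and it may be small if few patients are expedited. The 30-day measure is the more exposed of the two to leads of a month or more, because such a lead removes the affected patients from the early deaths altogether.

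This should be fixed. It is not a defect in the primary question, and it does not mean that an observed survival gain would be false, only that this comparison alone could not show that it was real.

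**What to change.** 1. In Secondary outcomes and Data analysis, state that survival from diagnosis is subject to lead time and is not by itself evidence that deaths were postponed.
2. Pre-specify a lead-time-adjusted sensitivity analysis for 30-day and 1-year survival over a stated range of lead times and shares expedited, including the rule for patients who die within the assumed lead. Reporting which combinations would alone account for the observed difference would make it easy to read.
3. In Health economics, run the analysis with the adjusted as well as the unadjusted survival and report both.
4. Where the data can be obtained, add deaths per 100 000 registered patients by arm, from 1 April 2022 to a fixed calendar date, using the mixed-effects Poisson model already planned for rates. Treat this as supportive evidence, not as a condition for reporting a survival difference: the rate is insensitive, and using it as a gate could suppress a real benefit.

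**Cost.** Items 1 to 3 need some extra analysis and no new data. Item 4 may need a further data request, since the article plans only all-cause deaths for its survival outcomes, which cover diagnosed patients. Cause-specific deaths would require cause of death; all-cause deaths would be more diluted. In either case the rate includes deaths among patients diagnosed before the trial. The changes are best settled before outcome data by arm are seen.

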
### Data collection

All primary and secondary outcome measures are available from NCRAS, Diagnostic Imaging Dataset and publicly available practice level data, including Cancer Waiting Times data. We will be using depersonalised (pseudo-anonymised) data. The Public Health England Office for Data Release guidelines indicated that no legal gateway (eg, section 251 approval) will be necessary to obtain these data.

### Data analysis

All analyses will follow Consolidated Standards of Reporting Trials (CONSORT) guidelines for cluster-randomised and pragmatic trials. The primary analysis, exploring the proportion of patients with early-stage cancer at diagnosis, will use mixed-effects logistic regression with a random intercept for practice to accommodate the hierarchical nature of the data (ie, random allocation by practice, with participants nested within a practice). This regression will include trial arm at practice level, and will adjust for patient-level covariates known to be associated with stage (age, sex, quintile of the income domain from the Index of Multiple Deprivation (IMD) and cancer site),^37^ and the practice-level minimisation variable (national tertile of age–sex standardised 2-week wait referral ratio). We will further adjust the model at the practice level for list size, clinical IT system used, and Care Quality Commission overall rating, should these variables be associated with stage in preliminary analyses (even if not unbalanced with respect to trial allocation). Trial arm and covariates will all be entered as fixed effects. The degree of change in the percentage of patients diagnosed at a late stage in intervention practices will be investigated by exploring the marginal distributions of trial arm on the probabilities predicted by these models.

For the secondary outcome of the stage at diagnosis of six cancers without eRATs, we will repeat the above model including data on the six non-eRAT cancers as well as the six eRAT cancers. This model will use all the variables described above, plus an indicator variable for whether the cancer site has an eRAT, and an interaction term between this variable and trial arm. From this model, we will obtain odds ratios (with 95% CIs) for (i) the ‘spillover’ effect of having the intervention on cancer sites not included in the intervention, and (ii) for the relative effect of the intervention on stage for included cancer sites compared with those not included in the intervention.

Mixed-effects logistic regression models with a random intercept for practice will also be fitted for the other secondary binary outcomes; route to diagnosis, conversion rate and timeliness. These models will include trial arm as a practice-level effect, and will adjust at the patient level for age, sex and quintile of the IMD income domain, and at the practice-level for the minimisation variable (national tertile of age–sex standardised 2-week wait referral ratio). These analyses will also adjust at the patient level for cancer site (routes to diagnosis analyses) or for referral type (2-week wait analyses) as appropriate. The models will be further adjusted as in the main outcome variable analysis.

Time-to-event secondary outcomes (length of waiting time, survival) will be analysed using mixed-effects parametric survival models with a random intercept for practice, and all other variables added as fixed effects. These models will include trial arm as a practice-level effect, and will adjust for the same patient-level factors as described above (waiting times adjusted for referral pathway rather than cancer site as above), and the practice-level minimisation variable (national tertile of age–sex standardised 2-week wait referral ratio). The models will also use the same adjustment as the primary outcome measure. An appropriate distribution to model the baseline hazard will be used, as determined by a comparison of the Akaike information criteria under different distributions.^38^

For rate outcomes (number of 2-week wait referrals, cancers and imaging investigations), we will analyse the rates per 100 000 registered patients per year by age–sex strata using mixed-effects Poisson regression models including a random intercept for practice. These models will include trial arm as a predictor and will adjust for the age and sex of the strata, and at the practice level for the minimisation variable (2-week wait referral ratio) and deprivation (quintile of IMD overall score). The models will be further adjusted at the practice level for list size, clinical IT system used, Care Quality Commission overall rating, and for the age and sex case mix of practices should these covariates be found to be associated with the outcome (even if not unbalanced with respect to allocation). Case mix will be incorporated by including variables for counts of practice populations in different age–sex strata (5-year age groups by sex, excluding one age–sex stratum that can be determined once all others are known).

All the above analyses will combine data for the six eRAT cancers for each model. For outcomes related to 2-week wait referrals, data will be combined for all referral pathways relevant to the six eRAT cancers. To investigate whether the eRATs produce a spillover effect, whereby diagnostic activity is increased for other cancers, we will repeat all analyses using data for the six non-eRAT cancers combined for each model. Investigation of a spillover effect for 2-week wait referral outcomes will use data for all referral pathways combined.

Additional sensitivity analyses will be conducted for the primary outcome in order to explore moderation arising from practice-level characteristics, using interaction terms. Although the trial has not been powered to detect low-to-moderate subgroup differences, such as differences in a single cancer site, large interaction effects that differ with respect to the direction of effect across subgroups are of interest. The potential impact of missing staging data on the primary outcome will also be explored through use of multiple imputation methods making use of auxiliary variables, such as survival time, morphology and grade, to improve the missing at random assumption in line with previous work).^37^

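### The primary odds ratio is conditional on being diagnosed and staged, so it does not by itself show fewer advanced cancers, and no stage-specific rate is planned beside it

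*Protocol article*

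**What the plan says.** The primary objective is the percentage of newly diagnosed patients, at the six sites, who are stage 1 or 2 rather than 3 or 4 (Objectives). The analysis follows it: "The primary analysis, exploring the proportion of patients with early-stage cancer at diagnosis, will use mixed-effects logistic regression", with a random intercept for practice (Data analysis). The trial is sized by "using an OR of 0.8 for a cancer being diagnosed at stage 3/4 in the intervention arm compared with the control arm" (Sample size).

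How many cancers are found is an outcome in its own right. Secondary outcomes lists each practice's "number of patients diagnosed with the six eRAT cancers combined, and the total number of cancer cases". The matching analysis reads: "For rate outcomes (number of 2-week wait referrals, cancers and imaging investigations), we will analyse the rates", per 100 000 registered patients per year, by mixed-effects Poisson regression (Data analysis). Nothing there splits the cancer rate by stage. The sensitivity analyses described for the primary outcome cover moderation by practice characteristics and missing stage. Survival is measured from the date of diagnosis (Secondary outcomes), and the cost-effectiveness analysis rests on the primary outcome and survival (Health economics).

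**The concern.** Randomisation makes the registered populations of the two arms comparable. It does not do the same for the patients diagnosed within them, because diagnosis comes after randomisation and the intervention exists to act on it. If eRATs add early-stage diagnoses, the advanced share falls even when the number of advanced cancers is unchanged. If they bring forward advanced cancers that would otherwise have been diagnosed after the window, the advanced share rises.

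The same OR can therefore describe different events in the population: advanced disease replaced by early disease, extra early disease, or a mixture. These differ in their meaning for patients and for cost-effectiveness. Survival does not settle the matter, since it is also conditional on diagnosis.

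**Working it through.** **Inputs.** The target OR for stage 3/4 is 0.8 (Sample size). The baseline early share comes from Primary outcome: "though for the six eRAT cancers, it is 35" per cent, so 65% are advanced. The mean cluster is 23 staged cancers, with 239 practices and 5497 patients per arm (Sample size).

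**The plan's own figures.**
- Odds of advanced stage are 65/35 = 1.857. Multiplied by 0.8 they are 1.486, a share of 59.8% and a fall of 5.2 points. The article gives 4.8 points as an incidence-weighted figure over the six sites. Averaging over sites with different shares gives a smaller figure than the pooled one, so this is no contradiction.
- Design effect: 1 + ((0.7² + 1) × 23 − 1) × 0.05 = 2.66, as stated. 2049 × 2.66 = 5450, against 5497 stated (0.9% apart). 5497/23 = 239.
- The starting figure of 2049 per arm cannot be rebuilt from pooled shares (1801 for OR 0.8; 2134 for 65% against 60.2%). It needs site-specific shares that the article does not give. The point here does not depend on it.

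**Same OR, different events.** Per 100 control-arm cancers (65 advanced, 35 early), suppose s advanced cancers are avoided. The early count E that keeps the OR at 0.80 is E = (65 − s)/1.486.

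| Advanced avoided (s) | Advanced | Early | Total | OR | Advanced rate ratio |
|---|---|---|---|---|---|
| 0 | 65 | 43.75 | 108.75 | 0.80 | 1.00 |
| 2 | 63 | 42.40 | 105.40 | 0.80 | 0.97 |
| 4 | 61 | 41.06 | 102.06 | 0.80 | 0.94 |
| 5.23 (pure stage shift) | 59.77 | 40.23 | 100 | 0.80 | 0.92 |

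The advanced share is 59.8% in every row. The first row needs 25% more early cancers: 23 × 0.35 × 0.25 = 2.0 per practice, or 5497 × 0.35 × 0.25 = 481 per arm. If the baseline early share were 30% to 40%, the rise in the total would be 7.5% to 10%. In the other direction, 5 extra advanced cases per 100 give (70/35)/(65/35) = 1.08.

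**What the planned total rate would show.** For 239 practices per arm, SE(log rate ratio) ≈ √(2 × (1/23 + k²)/239), where k is the between-practice coefficient of variation of true rates. The article does not give k; I assume 0 to 0.3, so the SE is 0.019 to 0.033. Power is Φ(log RR/SE − 1.96):
- total up 8.75%: 99% to 71%
- total up 5.4%: 79% to 35%
- total up 2.1%: 19% to 9%

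**What a stage 3/4 rate model would show.** Replacing 1/23 by 1/(23 × 0.65) gives SE 0.024 to 0.036. Power for the rate ratio of 0.92 under a pure stage shift is 94% to 64%. With a true ratio of 1, the 95% interval would have a half-width of 0.046 to 0.071 on the log scale.

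**The case against.** The primary analysis matches the stated objective, which is a percentage among newly diagnosed patients. The article justifies the split as common and as a national target metric. That stands: there is no contradiction, and no reason to replace the primary outcome.

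A reader might infer that the plan expects eRATs to change the number of cancers diagnosed. It does not say so. Its hypothesis is expedited diagnosis, and the number diagnosed is something to investigate. The denominator can change; whether it will is open.

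A reader might also infer that a stage shift cannot be told apart from a changed denominator. That is too strong. The article plans the total eRAT-cancer rate, and marginal predicted stage probabilities by arm. Their product gives a rough advanced-cancer rate ratio: in the extreme case 1.0875 × 59.8/65 = 1.00, which exposes the absence of benefit. What remains missing is a planned estimate with an interval, and the smaller rises in the mixtures would be hard to see in the total rate alone.

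The extreme case is not a forecast. Nothing in the article suggests 25% more early cancers. Some extra early diagnoses might have become advanced after the window, so no advanced cancer avoided means none within it. Diagnoses brought forward into April and May 2022 also drop out of the count, because data collection opens on 1 June 2022.

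Lastly, this is a condensed article, and an SAP that is not shown may hold such an analysis. That is possible. But the article itself lists the outcomes and the rate models, and stage-specific rates are not among them.

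**Conclusion.** The point holds in limited form. The primary OR is a valid answer to the stated objective, but it is conditional on a post-randomisation event that the intervention can change. At the article's 35% early share, an OR of 0.80 is compatible with anything from no advanced cancer avoided (total up 8.75%) to 5.2 avoided per 100 (total unchanged). The total rate would probably reveal the extreme, but probably not a rise near 2%. No analysis in the article estimates the stage 3/4 rate directly.

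The ORs are crude, whereas the planned model is adjusted and practice-conditional; the reasoning carries over, the exact figures may not. The power figures rest on the assumed range for k and treat the 23 staged cancers as the count per practice.

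It is tempting to conclude that a favourable OR should count only if the stage 3/4 rate is lower. The documents do not support such a gate. It has no precision criterion, and advanced cases brought into the window would raise that rate and make the rule misread them as failure.

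**What to change.** Keep the primary outcome and its model. Add two pre-specified secondary analyses: the rates of stage 3/4 and of stage 1/2 diagnoses of the six eRAT cancers per 100 000 registered patients by arm, each fitted with the mixed Poisson model already set out under Data analysis. State how unstaged cases enter, either through the multiple imputation already planned for stage or as a separate category. State that the OR will be interpreted jointly with both stage-specific rate ratios, the total rate ratio and their confidence intervals, with no rule that makes the conclusion depend on the stage 3/4 rate being lower. Fix this before outcome data are seen.

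The cost is two further models on data already requested, plus extending the imputation to them if that option is chosen. The drawback is that the rate comparisons are less precise than the proportion, because cancer incidence varies between practices.
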